### Acceptability

To examine the acceptability of iCT-SAD, we will also evaluate the dropout rate, rates of module completion, and participants’ feedback about their experience with the intervention.

### Participant timeline {13}

Participant enrolment will proceed in three stages as described below.

### Stage 1

Psychiatrist discusses the trial with a potential participant and makes a referral to the trial team if appropriate. They provide relevant contact details, clinical assessment information, and confirmation that they are able to provide ongoing TAU throughout the trial. The trial office will then send the potential participant the trial information, eligibility screening questions, and initial questionnaire pack to complete and return. Eligible participants are then invited for an assessment session.

### Stage 2

The assessment session is conducted by one of the trial therapists in person or via videoconference. It will confirm the primary diagnosis of SAD using ADIS-5, assess comorbid conditions using the Structured Clinical Interview for DSM-5 Disorders (SCID-5) [27], and assess eligibility criteria, risk, and current medication. Informed consent will be taken electronically. The trial team will then discuss whether the participant is eligible.

### Stage 3

The trial office will contact the participant to inform them whether they are eligible to take part, and if so, to confirm that they are still willing to participate and proceed with randomisation. If they agree to proceed, the assessor will inform the trial office for randomisation. The assessor will inform the participant of the allocation. A trial therapist is then assigned and appointments are arranged. For an overview of the trial procedure, see Table 1 (time schedule) and Fig. 1 (flow diagram).

**Table 1 Tab1:** Schedule of enrolment, treatments, and assessments

PHASE		Screening and baseline assessment	Allocation	Post-allocation		
				Treatment phase		Follow-up phase
TIMEPOINT		Baseline (week 0)		Mid-treatment (week 8)	Post-treatment (week 15)	3-month FU (week 27)
ENROLMENT	Eligibility screen	X				
	Informed consent	X				
	Demographics	X				
	Allocation		X			
INTERVENTION	iCT-SAD + TAU			➡	➡	➡
	TAU			➡	➡	
ASSESSMENTS	Questionnaires	X		X	X	X
	ADIS-5 SAD	X			X	X
	Adverse events			X	X	X
	Current medication	X		X	X	X
	Acceptability and feedback					X

*FU* follow-up, *iCT-SAD* internet-delivered version of cognitive therapy for social anxiety disorder, *TAU* treatment as usual, *ADIS-5* Anxiety and Related Disorders Interview Schedule for DSM-5, *SAD* social anxiety disorder

**Fig. 1 Fig1:**
[figure not shown]
Flow diagram of the trial. iCT-SAD internet-delivered version of cognitive therapy for social anxiety disorder, TAU treatment as usual, FU follow-up

### Sample size {14}

Sample size was calculated a priori for the between-group comparison of LSAS scores from baseline to post-treatment. The controlled effect size (Cohen’s *d*) observed in a previous randomised controlled trial of iCT-SAD compared to a waitlist control group with continuing primary care in the UK [8] was 2.2, which equates to a mean difference of 44 LSAS points. However, as the present trial uses a different population and cultural setting and is the first randomised controlled trial of iCT-SAD translated into another language, we used a conservative estimated mean difference of half this value (22 points). This calculation (using *β* = 0.9, *α* = 0.05, and a LSAS standard deviation of 19) indicated a required minimum sample of 16 participants per arm. Given the planned analyses of secondary measures and allowing for attrition (up to 20% dropout), we need 30 participants per group, making a total sample size of 60 to ensure the trial is fully powered to answer the research questions.

### Recruitment {15}

Participants will be recruited from psychiatric institutions in Japan, via referrals from their primary psychiatrist. To ensure sufficient participant recruitment, the trial will be promoted via trial therapists’ networks and relevant medical institutions using posters, leaflets, and digital media.

## Assignment of interventions: allocation

### Sequence generation {16a}

Participants will be randomly assigned to either the intervention or control arm at a ratio of 1:1, with the assignments made by the Internet Data and Information Center for Medical Research (INDICE) cloud, provided by the University Hospital Medical Information Network (UMIN). Randomisation will be stratified by baseline LSAS severity (≥ 78 or less). A minimization algorithm will be used to ensure a balance between arms.

### Concealment mechanism {16b}

The random allocation will be carried out by the UMIN INDICE cloud, an internet-based central randomisation system. Allocation concealment will be ensured, as the allocation result for each participant will not be visible to the trial team before they have been assigned to one of the treatment arms.

### Implementation {16c}

Once an eligible participant has agreed to participate, the assessor will inform the trial office. An independent research assistant will access the UMIN INDICE cloud and enter the necessary baseline information. The random allocation to either arm will be centrally generated. The trial office will inform the therapist of the allocation result and the therapist will then contact the participant.

## Assignment of interventions: blinding

### Who will be blinded {17a}

Owing to the nature of psychological interventions, it is not possible to blind participants or therapists to the intervention condition. A qualified independent assessor who conducts ADIS-5 for SAD at the post-treatment point will be blinded to the intervention condition.

### Procedure for unblinding if needed {17b}

The independent assessor of ADIS-5 for SAD will remain blinded throughout the trial. No other blinding is planned so unblinding will not occur.

## Data collection and management

### Plans for assessment and collection of outcomes {18a}

All participants will be given baseline questionnaires through an online survey platform. Settings will be used to alert participants to items they have missed and require a response to prevent missing data. Participants in the intervention arm will complete questionnaires using the iCT-SAD programme. Participants in the control arm will complete questionnaires through an online survey platform, with email reminders from the trial office. Japanese language versions of the below questionnaires will be used.

LSAS (primary outcome) is a 24-item scale with two subscales, fear/anxiety and avoidance of social situations. Each item is rated on a four-item Likert scale ranging from 0 (no fear/never avoidance) to 3 (high fear/usually avoidance), with lower scores indicating a better outcome. The Japanese version of LSAS has good internal consistency and construct validity [28, 29].

SPWSS is a 6-item scale of self-focused attention, anticipatory processing, post-event processing, and other variables, with each item rated on a scale from 0 to 8 [20].

SCQ is a 22-item scale that assesses the most common negative automatic thoughts related to SAD [20]. Each thought is rated in terms of how often it occurred in the last week and how much it is believed. The mean scores for frequency (mean ranges from 1 to 5) and for belief (mean ranges from 0 to 100) are computed separately, with lower scores indicating a better outcome.

PHQ-9 is a validated scale for assessing depressive symptoms [22, 23]. This scale contains 9 questions answered on a 4-point Likert scale, with numbers from 0 (not at all) to 3 (nearly every day). A higher score reflects more severe symptoms.

GAD-7 is a validated questionnaire commonly used to assess generalised anxiety symptoms and their severity [24, 30]. This scale consists of 7 questions answered on a 4-item Likert scale, with numbers from 0 (not at all) to 3 (nearly every day). A higher score reflects more severe symptoms.

WSAS is a five-item scale that measures perceived functional impairment across five domains: work, home management, social leisure activities, private leisure activities, and relationships with others [26]. Each item is rated on a 9-point severity scale ranging from 0 (not at all) to 8 (very severely), based on the degree to which the issue impedes one's ability to perform an activity. The Japanese version of the WSAS has good internal consistency and construct validity [31].

SBQ is a 29-item scale that assesses the extent to which patients engage in a range of common social anxiety related safety behaviours [20]. Each of the 29 behaviours are rated on a 4-point scale ranging from 0 (Never) to 3 (Always), with lower scores indicating a better outcome.

SAQ is a 50-item scale that assesses a range of common beliefs about oneself and social interactions that are thought to make individuals vulnerable to SAD [20]. The beliefs fall into three broad categories: ‘Excessively high standards for social performance’, ‘Conditional Beliefs’ and ‘Unconditional Beliefs’. Each item is rated on a 7-item Likert scale ranging from 1 (Totally disagree) to 7 (Totally agree), with lower scores indicating a good outcome.

Social participation and social satisfaction are measured with Alden and Taylor’s scales [21]. Social participation has 13 items that ask about the frequency of participation in social interactions, events, and conversations in the last month. Each item is rated from 1 (not at all) to 7 (frequently). Social satisfaction has five items that ask about satisfaction with relationships with colleagues, friends, and partners in the last month. Each item is rated from 1 (not satisfied at all) to 7 (very satisfied).

### Plans to promote participant retention and complete follow-up {18b}

Participants will be in regular contact with their primary psychiatrist and/or iCT-SAD therapist, who will provide support and encouragement, and are available to discuss any concerns participants may have about treatment or trial participation. Trial information and initial assessment procedures will clarify the timescale of treatment and explain the clinical importance of receiving a full ‘dose’ of iCT-SAD. Any participants who withdraw early from either arm will be invited to complete follow-up questionnaires at the relevant remaining principal time points.

### Data management {19}

Most of the data gathered online and saved to a database will be coded automatically. Metadata about participants’ activity on the iCT-SAD programme (e.g. time spent on different parts of the programme) will be automatically recorded. As most of the data will be collected automatically via secure online platforms specifically designed for research purposes, high data quality will generally be guaranteed. Only a small fraction of data (e.g. baseline demographic data, diagnostic assessment by an independent assessor) will be entered and uploaded to a secure server by the assessor or the trial office. The trial office will regularly check the overall data quality and completeness.

### Confidentiality {27}

Personal information of potential and enrolled participants will be collected and stored on a secure server available only to the trial office. Participant’s name, telephone number, and e-mail address will be informed only to the trial office and the trial therapist who will be assigned to them. Upon enrolment, each participant will be assigned a unique participant identification number for use in the data files created for the analysis. Data are kept in a secured storage and only authorised researchers or staff at the trial office are granted access by the principal investigator.

The iCT-SAD programme has numerous security features representing current best practice and complies with high data security standards. It employs secure client–server communication, full encryption of the server database, enforcement of strong passwords, two-factor authentication, and hosting on a tier 4 hosting server. External access to the database using the Secure Shell Protocol is prohibited. The system has been subjected to industry-standard penetration testing. Online data are secured by encryption to prevent access from outside parties. Access to the server data by the software company hosting the online therapy programmes (Whiskered Wizard) is protected by non-disclosure agreements and the Data Protection Act.

### Plans for collection, laboratory evaluation, and storage of biological specimens for genetic or molecular analysis in this trial/future use {33}

Not applicable. See the above item 26b; there will be no biological specimens collected.

## Statistical methods

### Statistical methods for primary and secondary outcomes {20a}

A separate statistical analysis plan (SAP) will be developed and approved by the trial team and an independent statistician before the database is locked. A detailed SAP will be uploaded to the trial registry (ISRCTN82859645). A brief overview of these analyses is given below.

Statistical analysis and reporting of this trial will be conducted in accordance with CONSORT guidelines, with the primary analyses based on the intent-to-treat principle without imputing missing observations. All statistical tests will be two-sided, and the level of significance will be set to 0.05. For the baseline variables, summary statistics are constructed employing frequencies and proportions for categorical variables and mean and standard deviation for continuous variables.

Linear mixed effect models will be used to analyse the primary and continuous secondary outcome measures. Time (mid, post), treatment arm (TAU + iCT-SAD, TAU alone), and the time-by-arm interaction will be specified as categorical fixed factors, with the stratification variable (baseline LSAS) as a fixed covariate and participant as a random effect. For the analysis of secondary outcome measures, the baseline score of the analysed measure is also included as a fixed covariate.

Standardised between-group effect sizes will be calculated by dividing the adjusted group difference by the baseline standard deviation of the whole sample. Standardised within-group effect sizes will be calculated from separate models that use the baseline score as a timepoint rather than a covariate.

Categorical secondary outcome measures (loss of diagnosis, response to treatment, and categorical acceptability outcomes) will be analysed using Fisher’s exact test. All other results will be reported descriptively.

Benchmarking will be performed through descriptive comparisons of the present results in relation to previous studies of iCT-SAD in the UK and Hong Kong [8, 9, 11, 12].

Baseline clinical and demographic characteristics will be examined as moderators of treatment outcomes by running linear mixed effect models (iCT-SAD + TAU only) with each candidate moderator added.

Mediation models will examine candidate mediators of the relationship between randomisation (treatment arm) and post-treatment LSAS scores following the procedure described by Freeman et al. [32]. The candidate mediators will be negative social cognitions (SCQ), safety behaviours (SBQ), self-focused attention (the general self-focused attention item of the SPWSS), rumination (the rumination item of the SPWSS), and depressed mood (PHQ). Mid-timepoint scores are used as the mediator, and post-treatment LSAS scores as the outcome. All models include baseline LSAS and baseline mediator scores as covariates.

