## Trial design {8}

This trial employs a two-arm, parallel-group, superiority randomised controlled design, comparing Japanese iCT-SAD in combination with treatment as usual (iCT-SAD + TAU) to TAU alone. Participants will be allocated using a 1:1 ratio. Participants will not be blinded to treatment allocation.

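### Fisher's exact test is valid but conservative for the binary secondary outcomes; Boschloo's exact test keeps the same 5% ceiling and is never less powerful (an optional gain of about 0 to 10 points)

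*Protocol article*

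**What the plan says.** The statistical methods section {20a} of the protocol article fixes both the level and the test. On the level: "All statistical tests will be two-sided, and the level of significance will be set to 0.05". On the test: "Categorical secondary outcome measures (loss of diagnosis, response to treatment, and categorical acceptability outcomes) will be analysed using Fisher’s exact test".

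The sample size section {14} gives the numbers available: "Given the planned analyses of secondary measures and allowing for attrition (up to 20% dropout), we need 30 participants per group". The trial design section {8} sets equal allocation. Section {20a} describes the analysis as "with the primary analyses based on the intent-to-treat principle without imputing missing observations", and the article does not say how a missing post-treatment ADIS-5 is counted. The denominators for these tests may therefore be completers, anywhere from 24 to 30 per arm.

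The blinding sections {17a} and {17b} make the post-treatment ADIS-5 assessor the only blinded party. Response is a percentage improvement on the self-report LSAS, so it is not blinded. The article states no expected rate and no power for any binary outcome.

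**The concern.** Fisher's test conditions on both margins of the 2x2 table. With a few dozen participants per arm its p-values take few distinct values, and the true rejection rate under the null falls short of the level set. The shortfall costs power.

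This matters most for loss of diagnosis. The primary outcome is self-report from unblinded participants, so the blinded diagnostic interview is the one between-arm result protected from reporting bias. The sample was also raised beyond the LSAS requirement partly for the secondary measures. If another exact test offers the same error guarantee with more power, using Fisher's gives up some of that sample's value on this outcome.

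**Working it through.** **1. The plan's own figure.** Section {14} uses a difference of 22 points and an SD of 19; I read its 0.9 as power. The normal formula is n = 2(z₀.₉₇₅ + z₀.₉₀)² × SD²/difference² = 2 × (1.960 + 1.282)² × 19²/22² = 15.7, so 16 per arm, as stated. Allowing for 20% dropout, 16/0.8 = 20; the rest of the 30 is attributed to secondary analyses. There is no stated figure for the binary outcomes to reproduce.

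**2. Inputs for the binary outcomes.** Two-sided 0.05 and Fisher's test come from {20a}. There are 30 per arm, or 30 × 0.8 = 24 per arm if dropout is 20% in both arms. The rates are my assumptions.

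**3. True error rate of Fisher's test.** For arm sizes n₁ and n₂ and a common rate π, size(π) = Σ Bin(x; n₁, π) × Bin(y; n₂, π), summed over all tables (x, y) with two-sided Fisher p ≤ 0.05. I enumerated every table and maximised over π.

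**4. Boschloo's test.** It uses Fisher's p-value as its statistic and rejects when p ≤ c, where c is the largest cut-off whose maximum size over π stays at or below 0.05. At all the arm sizes below c exceeds 0.05, so every Fisher rejection is also a Boschloo rejection.

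| Analysed per arm | Fisher, maximum size | Boschloo cut-off c | Boschloo, maximum size |
|---|---|---|---|
| 30/30 | 2.7% | 0.069 | 4.7% |
| 24/24 | 2.9% | 0.080 | 4.9% |
| 25/25 | 3.3% | 0.079 | 4.6% |
| 29/30 | 3.6% | 0.060 | 4.7% |
| 24/30 | 3.4% | 0.059 | 4.8% |
| 24/25 | 4.4% | 0.062 | 4.6% |

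Over all 28 pairs of arm sizes from 24 to 30, Fisher's maximum is below 3% in only 6, all with equal arms. Every unequal pair lies between about 3.4% and 4.4%. At a common rate of 10% Fisher's true error is lower still: 0.9% at 30/30 and 1.7% at 24/24.

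**5. Power, Fisher versus Boschloo, under assumed rates.** The first rate and the first arm size belong to iCT-SAD + TAU.

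| Rates | 24/24 | 30/30 | 24/30 | 24/25 |
|---|---|---|---|---|
| 50% vs 20% | 49.3 vs 59.2 | 59.6 vs 67.1 | 56.9 vs 63.2 | 57.2 vs 60.4 |
| 60% vs 25% | 62.0 vs 70.0 | 71.9 vs 79.3 | 67.0 vs 75.4 | 70.0 vs 70.4 |
| 40% vs 10% | 60.2 vs 66.4 | 70.5 vs 74.3 | 69.1 vs 72.2 | 65.8 vs 71.8 |
| 65% vs 10% | 98.1 vs 99.0 | 99.5 vs 99.7 | 99.2 vs 99.4 | 98.9 vs 99.2 |

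Over a wider grid (control rates 5% to 30%, treatment rates up to 85%) the largest gain was 9.9 points at 24/24 and 9.4 points at 30/30.

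**6. A scenario tied to the design effect.** As an illustration, shift a normal latent score by 22/19 = 1.16 SD. Control rates of 15%, 20% and 25% become about 55%, 62% and 69%. At 30/30, Fisher's power is 87%, 89% and 90%, against 91%, 93% and 94% for Boschloo's.

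**The case against.** Fisher's test is a valid, conventional choice for small samples. The 0.05 in {20a} is a ceiling, and the test respects it. The obvious alternative, an uncorrected chi-square, does not: its maximum true error is 5.5% at 30/30 and 6.0% at 24/24. All of this stands.

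A reader might infer that the true error rate is under 3% at this trial's size. The article does not support that in general. It allows up to 20% dropout and plans no imputation, so unequal denominators are likely, and every unequal pair from 24 to 30 gives more than 3%; so does 25/25.

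A reader might also infer that Fisher's test costs as much power as the whole planned attrition, because for 50% versus 20% Boschloo's at 24/24 (59%) roughly equals Fisher's at 30/30 (60%). That is a best case for Boschloo's at exactly equal arms. With one more control participant (24/25) the gap shrinks from 10 points to 3.

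It can also be said that effects as large as the one used to size the trial leave power high under either test, as step 6 shows. This too stands: the gain there is 3 to 4 points. Finally, these are secondary outcomes with no stated power, so no promised power is missed.

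What remains is that Boschloo's test gives the same guarantee and its power is never lower.

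**Conclusion.** The plan states nothing false here and its test is valid. Naming Boschloo's test is an optional efficiency improvement on secondary outcomes, worth from near zero to about 10 points of power. The upper end needs moderate differences, and the largest gains found were at equal analysed arms. Very large effects, or splits such as 24/25 under some rates, leave almost nothing to gain.

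The error rates depend only on the arm sizes. The power figures rest on assumed rates and on denominators between 24 and 30 per arm, which the article does not settle.

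The argument from blinding applies to loss of diagnosis alone. A reader might extend it to response, which is tested the same way, but response is derived from the self-report LSAS. The primary LSAS comparison is unaffected.

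**What to change.** In {20a} and the SAP, name Boschloo's unconditional exact test (two-sided, 0.05) in place of Fisher's for the two-arm 2x2 comparisons, and report the risk difference with a 95% confidence interval beside each p-value. Fisher's p-value can be kept as a footnote.

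This takes one sentence in each document and needs no extra data or participants; the test is in standard software. Section {20a} says the SAP is to be approved before database lock, so the choice can be made there without sight of results. The only downside is that the test is less familiar to readers.

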### Methods for additional analyses (e.g. subgroup analyses) {20b}

No additional analyses are planned.

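### The protocol calls within-arm predictors of outcome moderators, although models fitted to the iCT-SAD + TAU arm alone cannot estimate moderation

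*Protocol article*

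**What the plan says.** Section {20a} of the protocol (statistical methods for primary and secondary outcomes) states: "Baseline clinical and demographic characteristics will be examined as moderators of treatment outcomes by running linear mixed effect models". The same sentence limits the data set and describes the model: "TAU only) with each candidate moderator added". Both the label and the single-arm analysis set are thus fixed in the protocol.

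The Objectives section {7} words the matching aim differently. It describes an exploratory look at whether baseline characteristics are associated with outcome in the iCT-SAD + TAU arm, and does not speak of moderation.

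No interaction between arm and a baseline characteristic appears elsewhere. The main model has time and treatment arm, "and the time-by-arm interaction will be specified as categorical fixed factors", with baseline LSAS as a covariate. Section {20b} adds only: "No additional analyses are planned". On testing, section {20a} says: "All statistical tests will be two-sided, and the level of significance will be set to 0.05".

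**The concern.** Moderation of a treatment effect is a statement about a contrast: the difference between iCT-SAD + TAU and TAU alone is larger or smaller at some values of a characteristic. With the TAU arm left out, neither an arm term nor an arm-by-characteristic term can be fitted. The model returns an association between characteristic and outcome among treated participants. That association mixes ordinary prognosis, regression to the mean and any true effect modification, and one arm cannot separate them.

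What is at stake is the conclusion drawn. A paper that follows the wording of {20a} could report that iCT-SAD works better for some clients when the same characteristic predicts outcome equally well under usual care. Such a statement could influence who is referred.

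**Working it through.** **1. What each data set identifies.** Let M be a baseline characteristic. Write the expected post-treatment LSAS as a1 + b1·M under iCT-SAD + TAU and a0 + b0·M under TAU alone. The treatment effect at M is

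(a1 − a0) + (b1 − b0)·M.

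Moderation is b1 − b0. The one-arm model estimates b1 only. If there is no moderation, b1 = b0, so a significant b1 is pure prognosis. If b1 = 0 and b0 ≠ 0, moderation is real but the one-arm model sees nothing. A characteristic-by-time term within the arm does not help, because change in a single arm is still uncontrolled.

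**2. Inputs from the protocol.** The Sample size section {14} gives a mean difference of 22 points, an SD of 19, 30 per arm and dropout of up to 20%. This leaves 30 × 0.8 = 24 per arm. Tests are two-sided at 0.05. The protocol gives no figure for the moderator analysis. Its own sample size figure, 16 per arm, reproduces: 2 × (19 × 3.2415 / 22)² = 15.67, rounded up to 16, where 3.2415 is the sum of the normal quantiles for two-sided 0.05 and 90% power. That figure does not bear on this point.

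**3. Input not in the protocol.** The correlation r between the characteristic and the outcome is an assumption. It should be read as the correlation left after adjustment for baseline LSAS. The range used is 0.1 to 0.5.

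**4. Purely prognostic factor, no moderation.** The check is simplified to one post-treatment outcome. The one-arm slope test was simulated and compared with the Fisher-z approximation:

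P(significant) ≈ Φ(δ − 1.96) + Φ(−δ − 1.96), with δ = atanh(r) × √(n − 3).

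For example, with r = 0.4 and n = 24, δ = 0.4236 × √21 = 1.941, which gives 49%.

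| r (assumed) | One arm, n = 24: simulated (Fisher z) | One arm, n = 30: simulated (Fisher z) |
|---|---|---|
| 0.1 | 7% (7%) | 8% (8%) |
| 0.2 | 16% (15%) | 18% (18%) |
| 0.3 | 31% (29%) | 37% (36%) |
| 0.4 | 51% (49%) | 61% (60%) |
| 0.5 | 73% (71%) | 83% (81%) |

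The arm-by-characteristic interaction test in both arms was significant in about 5% of simulated trials throughout, its nominal level.

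**5. True moderators.** The slopes are assumed, at 0.5 SD of outcome per SD of the characteristic.

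| Where the slope lies | One-arm test, n = 24 / 30 | Two-arm interaction test, n = 24 / 30 per arm |
|---|---|---|
| TAU alone only | 5% / 5% | 46% / 56% |
| iCT-SAD + TAU only | 61% / 72% | 37% / 45% |

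The two interaction rows differ because the simulated residual variance was smaller in the first scenario. In the first row the one-arm test does no better than chance. In the second it is often significant, but nothing in its output distinguishes that case from the purely prognostic one in step 4.

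**The case against.** The strongest reply is that the objective already asks the right question and the one-arm model answers it. Association within the treated arm is a predictor question, so only one word in {20a} is loose. On this view the percentages in step 4 are power to detect a real within-arm association, and they become errors only if the result is read as moderation. All of this stands, and it is why renaming the analysis is enough. It does not excuse the label, which tells the reader to draw exactly that reading. Nor does a separate SAP excuse it, since the protocol has itself fixed both the label and the analysis set.

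The reply also notes that interaction tests would be weak at this size. Step 5 confirms it: 37% to 56% for a slope difference of 0.5 SD. Adding them is therefore optional.

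Two stronger readings are tempting but unsupported. A reader might infer that every variable that predicts LSAS will be declared a moderator. The protocol sets no rule for declaring one and calls the work exploratory, so the risk applies only to factors that reach significance, at rates that depend on r. A reader might also infer that {20b} contradicts {20a}. Its natural meaning is nothing beyond what {20a} already lists, so there is no conflict.

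**Conclusion.** The point holds as a fault of labelling with a consequence for interpretation. Section {20a} promises moderators from models that can yield only predictors of outcome within iCT-SAD + TAU. That a one-arm model cannot estimate moderation follows from the algebra and needs no assumption.

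The size of the risk does rest on assumptions. For a single purely prognostic factor, the chance of a significant result that would then be mislabelled runs from about 7% to 73% with 24 in the arm and 8% to 83% with 30, across assumed residual correlations of 0.1 to 0.5. The upper end needs strong correlations that the protocol does not document. The simulation also replaces the two-timepoint mixed model with a single outcome.

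The analysis is secondary and exploratory. The week-15 LSAS comparison between arms is untouched.

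**What to change.** In {20a}, rename these analyses predictors of outcome within iCT-SAD + TAU, in line with the Objectives section, and state that no moderation claim will be drawn from them. This changes wording only.

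If moderation is to be claimed, add candidate-by-arm and candidate-by-arm-by-time terms to the two-arm primary model at weeks 8 and 15. Report the week-15 interaction with its 95% CI as exploratory, and state that it is imprecise with 60 participants. No new data are needed: both arms are assessed at baseline, week 8 and week 15, and only the week-27 follow-up is confined to the intervention arm. Section {20b} needs an edit only if these interaction models are added.
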